Building on promising results from individual and group ACT programs for psychosis, the ACT for Life program was adapted for public outpatient mental health services in Melbourne, Victoria, Australia [34]. A pilot of the adapted program, referred to as “Recovery ACT,” was implemented by public mental health service clinicians as part of their routine practice and evaluated using pre- and postgroup outcome measures together with qualitative feedback from facilitators and participating consumers [35]. Results from the uncontrolled pilot study involving 9 groups and 90 consumers demonstrated that the program and its evaluation were feasible, acceptable, and safe [35]. Significant increases in personal recovery, well-being, and psychological flexibility were observed from the start to the end of the program. The extent of consumer and clinician interest in the groups, both from the original agency and additional agencies, strongly indicated the feasibility of conducting a more extensive evaluation. Building on this momentum, our clinician-academic partnership agreed to conduct this more stringent trial by incorporating a waitlist control period and an established measure of personal recovery as the primary outcome.

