## Methods

### Participants and Study Setting

We plan to recruit a minimum of 160 adults (aged between 18 and 65 years) who enroll in a Recovery ACT group program at 1 of 4 public mental health service study sites in Melbourne (NorthWestern Mental Health, St Vincent’s Mental Health Service, Alfred Mental and Addiction Health, and Peninsula Health Mental Health Service). The target minimum number of participants at NorthWestern Mental Health is 95 participants, and 32 participants each at the other study sites. The overall recruitment target was based on the minimum sample size needed to complete the intended analyses and an anticipated 60% participant retention rate based on the pilot study [35].

The inclusion criteria are a primary file diagnosis of either schizophrenia spectrum disorder or other psychotic disorder, a mood disorder with psychotic features, or a substance-induced psychotic disorder; currently receiving outpatient mental health care at 1 of the study sites; and current enrollment in a Recovery ACT group program. The exclusion criteria are lack of capacity to consent to the evaluation; lack of proficiency in speaking and comprehending English; a file diagnosis of intellectual disability or borderline personality disorder.

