Facilitators will be clinical mental health staff employed at a participating public mental health service who, where possible, have participated in an introductory ACT workshop and completed training in Recovery ACT. The group is led by 2 facilitators, one of whom is experienced (ie, has previously led a Recovery ACT group program) and adheres to the Recovery ACT group program manual [39]. Facilitators will be invited to attend a minimum of 3 “Support and Supervision” sessions while facilitating a group. The goal of these sessions is to enhance fidelity to the Recovery ACT group program manual [39]. In addition, facilitators will complete a fidelity log after each group session.

There are no restrictions on concomitant care and interventions, as this is an unfunded evaluation of the Recovery ACT group program that is already offered in routine clinical care at the participating public mental health services. To participate in the Recovery ACT program, participants must be receiving care at the respective public mental health service. As such, participants will receive provisions for ancillary and posttrial care at the public mental health service. The potential risks related to the study are deemed minimal. Facilitators are responsible for participants’ clinical care during the group program, including distress related to study procedures. Participants have a key support clinician for out-of-group issues that may arise.

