### Statistical Methods and Sample Size

We intend to use an intention-to-treat sample to test a univariate latent growth curve model of the primary outcome from before the start of the waitlist period to the start of the group to the booster session in order to compare the trajectory over the waitlist period to the trajectory over the active treatment period. We selected this method of analysis to strengthen our estimations of associations due to the limitations of the nonrandomized study design chosen as the most realistic option for an evaluation of a program already in routine practice [51]. A minimum sample size of 90 is required to conduct the proposed growth curve structural equation model (5 observed variables and 2 latent variables) with an anticipated medium effect size (0.3), α set at .05, and power (1–β) at .80. Univariate latent growth curve models for each of the 5 secondary outcomes will also be tested. If there are sufficient data, we will test whether the trajectory of the 4 psychological flexibility process variables from the start of the group to the midpoint session (T1 to T2) is significantly associated with the trajectory of personal recovery (T2 to T4) using multivariate growth models. We do not predict a priori any differences associated with the study site. We intend to calculate the ICC after the data are collected to determine the relatedness of the data collected at different study sites.

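### Clustering is checked only by study site, after data collection and with no stated consequence, although treatment is delivered in therapy groups; if outcomes change together within groups, standard errors will be too small

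*Protocol article*

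**What the plan says.** Statistical Methods and Sample Size plans a univariate latent growth curve model of personal recovery, comparing the waitlist trajectory with the active-treatment trajectory, and the same type of model for each of five secondary outcomes. It predicts no site differences and then gives its one statement on dependence: "We intend to calculate the ICC after the data are collected to determine the relatedness of the data collected at different study sites". It does not say what will be done with that ICC.

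The sample size in the same section is 90, for an effect size of 0.3 with "α set at .05, and power (1–β) at .80". Participants and Study Setting raises this to a recruitment target of 160, citing the minimum needed for the analysis and "an anticipated 60% participant retention rate based on the pilot study". No allowance for clustering is mentioned in either place.

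The Abstract (Methods) and Intervention sections describe weekly sessions delivered to groups. On staffing, Intervention says "The group is led by 2 facilitators". The only guide to group size is in Background and Rationale: "Results from the uncontrolled pilot study involving 9 groups and 90 consumers".

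**The concern.** Members of one therapy group share facilitators, sessions and peers from the start of the program (T1). The article describes several ways in which groups may differ. Facilitators are trained where possible, supervision is by invitation, facilitators may help with questionnaires, and measures are mostly completed at group sessions, so members also share calendar dates. Any of these can make members' change after T1 more alike than that of people in different groups.

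A site ICC is not a substitute. With four sites it rests on 3 degrees of freedom, and it cannot show dependence among separate groups run at the same site.

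At stake are the confidence intervals and type I error for the primary outcome and all five secondary outcomes. The understatement falls mainly on the group-period slope, where improvement is predicted, and not on the waitlist slope, where no change is predicted.

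**Working it through.** **Inputs from the article.** Alpha 0.05 (taken as two-sided), power 0.80, effect 0.3, N = 90, recruitment 160, retention 60%, four sites, pilot of 90 consumers in 9 groups.

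**Assumptions.** Analysed group size m = (90/9) × 0.60 = 6. Therapy-group ICC of change ρ = 0.02, 0.05 or 0.10, with 0 as the reference.

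**1. The planned 90.** A one-sample (within-person) test of a standardised effect of 0.3 needs ((1.960 + 0.842)/0.3)² = 87.2. Adding the t correction 1.960²/2 = 1.9 gives 89.1, rounded up to 90. The closed-form lower bound on N for an effect of 0.3 in a structural equation model gives 89.12, also rounded up to 90. The article does not say which calculation was used. Both assume independent participants and neither has a clustering term.

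**2. The margin in 160.** 160 × 0.60 = 96 analysable. 96/90 = 1.07, so the spare covers a group ICC of at most (1.067 − 1)/5 ≈ 0.013 at six per group.

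**3. Group-period slope.** Design effect DE = 1 + (m − 1)ρ. True SE / naive SE = √DE. Actual two-sided error = 2[1 − Φ(1.960/√DE)]. Power at N = 90 is Φ(2.802/√DE − 1.960), reading the effect of 0.3 as the group-period slope, since the article does not tie it to a parameter.

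**4. Waitlist-versus-active contrast.** Suppose residuals are independent with equal variance σ², the two periods are about equal in length, and a group component with variance τ² acts only after T1. Then Var(T3 − T1) = 2σ² + τ², and Var[(T3 − T1) − (T1 − T0)] = 6σ² + τ². A change ICC of ρ becomes ρ/(3 − 2ρ) for the contrast: 0.02/2.96 = 0.007, 0.05/2.90 = 0.017, 0.10/2.80 = 0.036. The design effects at six per group are 1.03, 1.09 and 1.18.

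| Change ICC | DE, slope | SE ratio, slope | Error, slope | Power at N = 90, slope | Error, contrast |
|---|---|---|---|---|---|
| 0 | 1.00 | 1.00 | 5.0% | 80% | 5.0% |
| 0.02 | 1.10 | 1.05 | 6.2% | 76% | 5.4% |
| 0.05 | 1.25 | 1.12 | 8.0% | 71% | 6.0% |
| 0.10 | 1.50 | 1.22 | 11.0% | 63% | 7.1% |

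**5. Check by simulation.** With 20,000 null trials of 96 people in groups of six, and the ICC applied to the tested quantity, a test ignoring groups rejected in 4.8%, 6.3%, 8.1% and 10.8% of trials at ICC 0, 0.02, 0.05 and 0.10. A test on group means rejected in 5.0%, 5.1%, 5.2% and 4.9%.

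**The case against.** The strongest reply is that the article condenses a longer protocol, its analysis plan is not shown, and levels of clustering are often left to such a plan. It never says that participants will be treated as independent, and naming site does not rule out the therapy group. That is fair as far as omission goes. But the article does name a unit for checking dependence, and it is not the unit in which treatment is delivered. A later plan would have to go beyond that sentence.

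A second reply is that participants serve as their own controls (Randomization and Blinding). This removes constant differences between groups. It does not remove group effects that arise after T1, which stay in the group-period slope and in the contrast. It does dilute them in the contrast, and that part of the reply stands.

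A third reply is that the ICC and group size are unknown, which also stands. At ICC 0.01 with six per group the error is only 5.6%. Consent to the evaluation is optional, so fewer than six may be analysed: with four per group and ICC 0.05, DE = 1 + 3 × 0.05 = 1.15 and the error is about 6.8%.

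A reader might also infer a rule under which the site ICC decides whether clustering is modelled. The text contains no such rule and attaches no decision to the ICC.

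**Conclusion.** The point holds conditionally. The article considers clustering at site level only, after the event and without consequence, and its sample size makes no allowance for therapy groups. If the therapy-group ICC of post-T1 change is above zero, a growth model without that level gives standard errors that are too small. At six analysed per group and an ICC of 0.02 to 0.10, error is about 6.2% to 11.0% for the group-period slope. It is about 6% to 7% for the waitlist-versus-active contrast at an ICC of 0.05 to 0.10. The contrast figures rest on the equal-variance illustration, and another variance structure would move them.

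Two stronger readings are not supported. One is that the standard errors are certainly too small: the article gives no ICC, and at zero there is no error. The other is that the primary comparison carries an error of 8% to 15%. Those figures belong to the group-period slope tested alone, and the upper end (15.5%) needs an ICC of 0.10 with all ten members of every group analysed, which does not fit 60% retention.

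**What to change.** Before any analysis, name the therapy group as the clustering unit in the primary model and the five secondary models. Use either standard errors clustered on therapy group with a small-sample correction, or a random therapy-group effect on the post-T1 slope. With about 15 groups (90/6) a random slope variance will be imprecise, so the choice and the correction should be stated in advance. Report the therapy-group ICC of change in place of relying on the site ICC. State that the 80% power at N = 90 assumes no group clustering, with the power column above as the range for the group-period slope. Site as a fixed effect is optional.

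The change is one of wording. Data Collection and Management lists attendance records and recruitment logs, from which group membership should be recoverable, and Results says that no analysis has been done. No extra recruitment is proposed. The cost is somewhat wider confidence intervals and a less favourable stated power.

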#### Randomization and Blinding

This study is a nonrandomized (unblinded) trial that uses a single group, waitlist control, and a quasiexperimental design. All participants serve as their own control. The data for all participants on change in outcomes over the waitlist period (no active intervention) will be used to compare with the data on change in outcomes during the active intervention. The planned statistical methods will strengthen our conclusions. The risk of researcher bias is lessened by the self-report format of the primary and secondary outcomes and the opportunity for participants to submit questionnaires in a sealed envelope.

#### Data Collection and Management

The data will be collected using deidentified hardcopies of all evaluation documents (quantitative questionnaires completed by participants and facilitators, copies of qualitative feedback forms, and demographic and clinical information forms), and other trial documents (attendance records, fidelity logs, and recruitment logs). Facilitators will assist participants with questionnaire completion if needed. As facilitators will serve a dual role as clinical service providers and study personnel, participants will be provided a sealable envelope to return deidentified self-report questionnaires that will be reviewed by study personnel other than their facilitators if sealed (either at the site or by the study coordinator). If a participant does not attend a group session when data are collected, facilitators will attempt to schedule an appointment to complete study measures.

Deidentified data from hard copy evaluation documents will be entered into a password-protected electronic file maintained on secure computers by the study coordinator. A coding sheet with identifiable participant information will be saved as a password-protected electronic file on the sponsor site’s server. Hard copies of consent forms and study documents will be kept in a locked filing cabinet at the Academic Psychology Unit located at the sponsor’s site.

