### Outcomes

#### Timeline

The schedule of enrollment, interventions, and assessments is displayed in Figure 2. The quantitative self-report outcome measures are intended to be completed independently at the start of the waitlist period (T0, approximately 4-6 weeks before the start of the group program, typically at the “Information and Engagement” session), at the start of the group program (T1), at the end of the group program (T3, which is 6 weeks after the start of the group program), and at the booster session (T4, about 10 weeks after the start of the group program). Some participants may complete outcome measures at the midpoint session (T2, which is 3 weeks after the start of the group program) if the study site is resourced to collect data at an additional time point. Measures are completed after the group session, except for at T1, when participants complete measures before the start of the group to ensure no exposure to the program’s content. Participants can request assistance from facilitators to complete the measures. Demographic and clinical information will be obtained from participants’ electronic health records at T0 and will include their date of birth, gender, ethnicity, country of birth, highest level of educational attainment, highest level of employment, current employment status, primary mental health file diagnosis, co-occurring mental health file diagnoses, date of first contact with mental health services, number of listed episodes of outpatient mental health care, and number of psychiatric admissions.

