#### Primary Outcome

The primary outcome is personal recovery, as measured by the 15-item version of the Questionnaire about the Process of Recovery (QPR) [40,41]. The 15-item QPR has good internal consistency (QPR total α=.89), fair to good test-retest reliability (QPR total intracluster correlation coefficient [ICC]=0.74), moderate sensitivity to change, and adequate convergent validity [42]. The QPR is a measure that assesses the 5 core processes of personal recovery that comprise the “Connectedness; Hope and optimism about the future; Identity; Meaning in life; and Empowerment” (CHIME) framework [43], which is currently the strongest conceptualization of personal recovery in serious mental illness. The Recovery ACT group program seeks to support change in these dimensions for participants.

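### Facilitators who run the group may help complete the outcome forms, and review by other staff is promised only for envelopes that participants choose to seal

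*Protocol article*

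**What the plan says.** The general rule stands under Timeline: "The quantitative self-report outcome measures are intended to be completed independently". The same section then allows an exception: "Participants can request assistance from facilitators to complete the measures". Data Collection and Management repeats it: "Facilitators will assist participants with questionnaire completion if needed". Neither statement limits the help to particular measures or time points.

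The helpers are the people who deliver the program. The Intervention section says: "The group is led by 2 facilitators". Data Collection and Management acknowledges the conflict with the words "As facilitators will serve a dual role as clinical service providers and study personnel" and answers it with a sealable envelope. Deidentified forms returned in it "will be reviewed by study personnel other than their facilitators if sealed". Randomization and Blinding describes the envelope as something participants have the chance to use, not as a requirement.

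Table 1 records that no masking is used. Randomization and Blinding nevertheless concludes: "The risk of researcher bias is lessened by the self-report format of the primary and secondary outcomes", and names the sealed envelope as the second mitigating feature. The primary outcome, the 15-item QPR, is one of these self-report measures.

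**The concern.** Self-report lessens researcher bias to the extent that the person with a stake in the result does not take part in the response and does not see it. Here the group's own therapist may take part in completion. The promise that someone else will review the form depends on each participant's decision to seal it. The protocol names the dual role and then leaves the safeguard optional.

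This matters because each participant is his or her own control, and the primary analysis compares the trajectory over the waitlist with the trajectory over treatment. A response effect that begins between T1 and T3 coincides with the change of phase and would look like benefit. With no concurrent control group, the growth model cannot separate the two.

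**Working it through.** The protocol gives no figure to reproduce on this point. The check sets the relevant statements side by side and then asks when a response effect would cancel.

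**Who can help or see the form, by time point** (Timeline; Data Collection and Management)

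| Time point | When completed | Facilitator's position |
|---|---|---|
| T0 | Typically at the information session, 4-6 weeks before the group | Involved, but no therapy delivered |
| T1 | Before the group starts | No therapy delivered |
| T3 | After the session, at 6 weeks | Has delivered the core program |
| T4 | After the booster session, at about 10 weeks | Has delivered the whole program |

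Help is allowed in every row. In every row, independent review depends on sealing. The optional T2 form, at 3 weeks, also falls after therapy has begun.

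**What the envelope covers.** A sealed envelope protects answers given alone. It does not protect answers given with the facilitator's help, because the facilitator was present when they were given. The two routes therefore need separate handling: sealing for one, a record of assistance for the other.

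**When the effect cancels.** Let b0, b1 and b3 be the mean shift in score from facilitator involvement at T0, T1 and T3. In simple differences (a simplification of the planned growth model that ignores unequal interval lengths):

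- bias in waitlist change = b1 − b0
- bias in treatment-period change = b3 − b1
- bias in the contrast = (b3 − b1) − (b1 − b0) = b3 − 2·b1 + b0

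If involvement shifts answers equally throughout (b0 = b1 = b3), the contrast is unbiased: b − 2b + b = 0. If the shift is b at T0 and T1 and b + d at T3, the bias is (b + d) − 2b + b = d. So only a differential effect matters. A wish to please the therapist after the therapy has been delivered is a plausible reason for d to be positive. The documents do not establish that it is.

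**Size.** If there is no shift at T0 and T1, d equals the share of forms affected times the shift per affected form. The documents give neither input. With an assumed share of 20-40% and an assumed shift of 0.2-0.4 SD, the result would run from 0.20 × 0.2 = 0.04 SD to 0.40 × 0.4 = 0.16 SD. This shows only how the two inputs combine. Both are assumptions, and the range is not an estimate for this trial.

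**The case against.** The strongest reply is that the protocol already deals with this. Independent completion is the rule and help the exception. Forms are deidentified, envelopes are supplied, sealed forms go to other personnel, and the data file is kept by the study coordinator. Randomization and Blinding claims only that bias is lessened, and the Discussion concedes that the design limits causal conclusions. All of this stands. There is no outright contradiction; a stated safeguard is left weaker than it need be.

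Four stronger readings are tempting, and the documents do not support them:

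- **Facilitators influence the answers.** Assisting may mean no more than reading items aloud or explaining the form.
- **Facilitators review unsealed forms.** This is inferred from the condition on sealing. The text neither says it nor rules it out.
- **Assistance goes unrecorded.** The article is silent, but evaluation procedure manuals exist (Data Monitoring and Adverse Event Reporting) and are not shown. They may contain rules or a log.
- **The bias certainly favours the program by a known amount.** Facilitators are also involved at T0, and need for help could be greatest at first completion. Courtesy responding after an open therapy can arise without any help, so the part due to these procedures is unknown.

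The objection to an outright ban on facilitator help also stands. The study is unfunded and relies on facilitators for evaluation tasks, and the obvious substitute, the key support clinician, is a treating clinician too.

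**Conclusion.** The point holds as a modest, avoidable weakness in outcome collection. The stated procedure lets the group's own facilitators assist with the primary questionnaire and guarantees review by others only for sealed forms. Any resulting response effect that starts after T1 could add to the treatment-period change relative to the waitlist. This rests on the effect being stronger after therapy than before it, which is plausible but not shown. A constant effect would cancel. No size can be stated from the documents.

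The statement that self-report lessens bias is not false, but it needs qualifying. The case for acting rests on how little the change costs, not on a demonstrated bias.

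**What to change.** 1. Make sealing the envelope the standard procedure at every time point. Have it opened only by the study coordinator or by site personnel not running that group; the protocol already foresees both for sealed forms.
2. Add a tick box to each form from now on: assisted, no or by whom. Note the date of the change.
3. Report a sensitivity analysis of the primary comparison that excludes or flags facilitator-assisted forms. Keep the intention-to-treat analysis primary, because excluding assisted forms selectively removes people who needed help.
4. Qualify the statement in Randomization and Blinding: self-report lessens researcher bias for forms completed alone and sealed, and less so for assisted or unsealed forms.

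Help from someone other than the group's own facilitators is preferable where existing staff allow, but it is not a condition of the fix.

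The cost is a line in the procedure manuals and one tick box, since envelopes are already supplied. The downside is a small change of procedure partway through collection. Forms already collected cannot be classified: at submission 93 people had consented, 65 had completed T1 and 40 had complete data. With a target of 160, at least 160 − 93 = 67 participants were still to be enrolled at that point, so later forms can still benefit.
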